## **Study outcomes**

### **Virological effects of intensified monitoring**

- Amount of drug resistance mutations per patient with therapy failure in each arm
- Selection of specific resistance mutations associated with multi-drug resistance in each arm
- Consequential loss of therapeutic options between arms
- Rate of virological failure in the absence of drug resistance between arms
- Rate of resuppression after detectable viremia in each arm
- Unnecessary treatment switches averted in the intervention arm and unnecessary therapy switches made in the control arm

- Loss of therapeutic options over time in the presence of a failing regimen in both arms
- The influence of genotypic resistance testing on the choice for a second line regimen in the intervention arm
- Time on a failing regimen per patient with therapy failure in each arm

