#### 5.1.2 Control arm follow-up – standard of care HIV treatment monitoring

300 patients randomly assigned to this arm will be monitored in full concordance with current South African NDoH guidelines in use at the study site. Viral load measurements will be performed at month 12 and 24 after start of ART (for newly initiated patients) or at month 12 and 24 after the last VL measurement (patients already on ART). If a VL >1000 copies/ml is detected, the patient is called back for counselling for therapy adherence and repeat VL measurement, 2 months after the initial VL measurement. If the repeat VL measurement is >1000 copies/ml after adherence counselling, this is taken to be indicative of therapy failure due to development of drug resistance and a switch to second line therapy is made, together with intensified adherence counselling, without verifying the cause of virological failure by

performing DLM or drug resistance testing. If VL drops to <1000 copies/ml after adherence counselling, the first line treatment is maintained. For a full overview of study visits and clinical algorithms in the control arm, see Figure 1: ITREMA study flowchart.

Sample collection in the control arm consists of storage of EDTA-derived plasma and a DBS at study baseline and at the subsequent study visits at month 3, 6, 9, 12, 15, 18, 21 and 24 of ART, as well as during any additional study follow-up visits in case of a VL >1000 copies/ml. Blood draws at baseline, month 3, 6, 12 and 24 after start of ART, and in case of follow-up after a VL >1000 copies/ml coincide with blood draws performed as part of standard of care. The following measurements will be performed on stored samples:

- An additional CD4 measurement at study month 6, in order to assess eligibility for randomisation and rate of CD4-count recovery.
- Retrospective VL testing on stored EDTA-derived plasma in case of clinical therapy failure, in order to retrospectively examine the duration of viremia.
- Retrospective drug resistance testing on stored DBS in case of clinical therapy failure to examine the accumulation of resistance mutations over time.
- Screening for transmitted drug resistance by drug resistance testing on stored DBS obtained as at baseline, prior to start of ART.

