### 5.1.3 Intervention arm follow-up – Intensified HIV treatment monitoring

300 patients randomly assigned to this arm will be monitored using the investigational intensified monitoring strategy. This strategy consists of 3-monthly VL monitoring at month 9, 12, 15, 18, 21 and 24 (after start of ART in initiating patients or after the last VL measurement in patients on ART). If a VL measurement > 1000 copies/mL is detected, the patient will be called back for a follow-up study visit at the next monthly medication collection visit (4 weeks after detection of elevated VL). Upon arrival DLM is performed, the VL measurement is repeated, and a DBS prepared and stored at room temperature. Procedures following this depend on the result of DLM:

- If drug levels are detected by DLM, the result of the VL measurement is awaited. If the repeat VL is >1000 copies/ml, the DBS is shipped directly by courier to the WHO reference laboratory for drug resistance testing. The reference laboratory will provide feedback by means of a digital resistance report to the coordinating research physician. The patient will be called back for a second follow-up study visit at the next monthly medication visit (8 weeks after detection of elevated VL), either for prescription of second-line therapy or continuation of first-line therapy, guided by the

result of resistance testing.

- If DLM at the first follow-up visit indicates that drug levels are not detected, intensified counselling is performed at the same visit and first-line therapy will be maintained, regardless of the result of the repeat VL measurement. The patient will not be called back and the next VL will be performed at the next scheduled three-monthly time point. However, if the VL result at this visit is again >1000 copies/ml, drug resistance testing will be performed regardless of the outcome of DLM.

For a full overview of study visits and clinical algorithms in the control arm, see Figure 1: ITREMA study flowchart.

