#### 5.2.4 Follow-up of elevated viral load measurement

##### 5.2.4.1 Intervention arm

In case of a VL >1000 copies/ml of a patient in the intervention arm, feedback of this result will be given by the clinical site laboratory after 2-5 working days). The patient will be notified to report back to the research clinician or nurse at his/her next monthly routine clinical visit for medication collection (day 28 after study visit). At this visit repeat viral load testing, DLM and collection of plasma and DBS is performed. If DLM indicates no detectable drug level (see “5.2.5 Drug Level Monitoring”), the patient is informed of this result, and intensified adherence counselling is performed. If DLM does not indicate non-adherence, standard of care adherence counselling will be performed. The result of the second VL will be available after 2-5 working days (day 31-33 after study visit). In case of a second VL >1000 copies/mL and a detectable drug level at DLM, the DBS will be sent to the WHO reference laboratory for drug resistance testing and patients will be notified again to report back to the research clinician or nurse at his/her next monthly routine clinical visit (day 56 after study visit) for genotype guided switch to second-line therapy or for genotype guided continuation of treatment combined with counselling in case no relevant resistance is detected. In case DLM detected no drug level, the DBS is not sent and genotyping not performed. The patient will not be called back and not be switched to second-line therapy prior to the next study visit. In case an elevated VL is again detected at the subsequent study visit (day 84 after previous study visit), a DBS is sent directly for drug resistance testing and genotype guided therapy switch or continuation is performed. In case of continuation, the three monthly monitoring frequency is maintained. In case of switch, a VL will be performed six months after the switch to evaluate initial therapy success. Three monthly study visits will be continued in an observational manner, at which storage of DBS and plasma is performed.

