## 6 OUTCOMES AND ANALYSIS OF RESULTS

### 6.1 Virological and clinical effects of intensified monitoring

Virological outcomes will be differences between arms in (1) the number of drug resistance mutations present, (2) the selection of specific resistance mutations associated with multi-drug resistance (presence of the K65R mutation, or the presence of >1 NNRTI mutation) and (3) consequential loss of therapeutic options. Furthermore, (4) the rate of virological failure in the absence of drug resistance in both arms, unnecessary treatment switches averted in the intervention arm and unnecessary therapy switches made in the control arm will be assessed. An averted case of unnecessary switching will be defined as two sequential elevated VL results in the intervention arm without presence of resistance mutations. Assessment of unnecessary switching in the control arm can be ascertained by retrospective genotypic resistance testing.

Additional virological outcomes will be (5) the time on a failing regimen, defined as the time during which viremia > 1000 copies/mL is maintained after the first instance of a viral load >1000 copies/ml (6) The loss of second line therapeutic options over time in the presence of a failing regimen. Comparison of the extent of drug resistance between both groups will allow for assessment of the clinical consequences of resistance development in both arms. (7) The influence of genotypic resistance testing on the choice for a second line regimen. Genotypic resistance testing results enable the physician to make an informed decision with regard to a follow-up regimen to the first-line regimen. By comparing the chosen regimens in the intervention and control groups, the effect of the availability of genotypic resistance data on clinical decision-making will be compared. These outcomes can be compared between both arms as VL and CD4 measurements will be performed retrospectively in the control group, resulting in an equal frequency of measurements between both arms.

Clinical outcomes will be decrease in CD4 count during failure, QoL as measured using a validated QoL questionnaire, and recorded events of patient morbidity and mortality that can be related to immunological failure.

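### The time-on-a-failing-regimen outcome is defined as duration of viraemia with no stop at the switch, so it counts second-line time and can dilute the difference between arms

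*Protocol*

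**What the plan says.** The Summary lists the outcome as "Time on a failing regimen per patient with therapy failure in each arm". Section 6.1 gives the working rule: "defined as the time during which viremia > 1000 copies/mL is maintained after the first instance of a viral load >1000 copies/ml". The rule has a start (the first VL above 1000) and a condition for continuing (viraemia above 1000), but it does not mention the change of regimen.

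The schedule that feeds this outcome is as follows.

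- **Control arm, before a switch** (5.1.2): "Viral load measurements will be performed at month 12 and 24 after start of ART", or after the last VL for patients already on ART. An elevated result leads to a "repeat VL measurement, 2 months after the initial VL measurement", and a second elevated result leads to the switch.
- **Intervention arm, before a switch** (5.1.3, 5.2.4.1): "3-monthly VL monitoring at month 9, 12, 15, 18, 21 and 24". With a confirmed VL above 1000 and drug detected, the patient returns at "his/her next monthly routine clinical visit (day 56 after study visit) for genotype guided switch to second-line therapy" if resistance is found.
- **After a switch:** 5.2.4.1 says "In case of switch, a VL will be performed six months after the switch to evaluate initial therapy success", and 5.2.4.2 repeats the sentence for the control arm. In both arms three-monthly visits continue observationally, with plasma and DBS stored.
- **Retrospective VL:** 5.1.2 lists for the control arm "Retrospective VL testing on stored EDTA-derived plasma in case of clinical therapy failure, in order to retrospectively examine the duration of viremia". Section 5.2.2 likewise confines it to control patients with therapy failure. The sample list in 5.1.3 stands under the intervention heading, although its text says control arm. It contains no retrospective VL.

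Section 6.1 then argues that the outcomes are comparable because retrospective testing gives both arms the same measurement frequency.

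**The concern.** The name and the rule describe two different quantities. Time on a failing regimen ends when the patient leaves that regimen or resuppresses on it. Duration of viraemia ends when viraemia ends, whichever regimen the patient is taking. In both arms the last measured VL before a prescribed switch is above 1000, so the two quantities differ for essentially every switched patient.

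The protocol's rationale is that failure is found and acted on sooner, and time to switch reflects that directly. The rule as written adds to each switched patient a period on second-line therapy whose length depends on when the next VL is read. Within a fixed follow-up, the added period can crowd out the difference. If the arms are also read at different times after the switch, the difference can shrink or change sign for reasons unrelated to the strategy.

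**Working it through.** The protocol gives no expected value or power for this outcome, so there is no planned figure to reproduce. The check is visit arithmetic in the protocol's 28-day months.

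**Inputs from the protocol.** Control clinical VLs at months 12 and 24, repeat two months later. Intervention VLs every three months, switch at day 56 (2 months). VL six months after a switch in both arms. Follow-up to month 24.

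**Assumptions.** First sample above 1000 equally likely at months 9, 12, 15, 18, 21 and 24. Every failure is switched. Drug is detected and resistance found in the intervention arm. The control switch is made at the repeat VL. Patients are suppressed 1 to 4 months after the switch.

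**Formulas.** Control switch month = next clinical VL (12 or 24) + 2. Intervention switch month = onset + 2. Time to switch = switch month − onset. Time under the written rule = month of first suppressed post-switch VL − onset.

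*Without truncation (months)*

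| Onset month | 9 | 12 | 15 | 18 | 21 | 24 | Mean |
|---|---|---|---|---|---|---|---|
| Control, to switch | 5 | 2 | 11 | 8 | 5 | 2 | 5.5 |
| Intervention, to switch | 2 | 2 | 2 | 2 | 2 | 2 | 2.0 |
| Control, VL 6 months after switch | 11 | 8 | 17 | 14 | 11 | 8 | 11.5 |
| Intervention, VL 6 months after switch | 8 | 8 | 8 | 8 | 8 | 8 | 8.0 |
| Control, stored plasma read 3-monthly, suppressed 2–4 months after switch | 9 | 6 | 15 | 12 | 9 | 6 | 9.5 |
| Control, the same, suppressed by 1 month | 6 | 3 | 12 | 9 | 6 | 3 | 6.5 |

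- Stopped at the switch: 5.5 − 2.0 = 3.5.
- Written rule, both arms read at six months: 11.5 − 8.0 = 3.5, unchanged.
- Written rule, control read three-monthly and intervention only at six months: 9.5 − 8.0 = 1.5, a loss of (3.5 − 1.5)/3.5 = 57%; or 6.5 − 8.0 = −1.5, a reversal.
- Written rule, both arms read three-monthly: the difference stays 3.5.

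Onset at month 12 isolates the reading effect. Both arms switch at month 14, so time to switch is 2 months in each. Under unequal reading with suppression at 2–4 months, control is 18 − 12 = 6 and intervention is 20 − 12 = 8.

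*Cut at month 24 (months)*

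| Onset month | 9 | 12 | 15 | 18 | 21 | 24 | Mean |
|---|---|---|---|---|---|---|---|
| Control, to switch | 5 | 2 | 9 | 6 | 3 | 0 | 4.17 |
| Intervention, to switch | 2 | 2 | 2 | 2 | 2 | 0 | 1.67 |
| Control, VL 6 months after switch | 11 | 8 | 9 | 6 | 3 | 0 | 6.17 |
| Intervention, VL 6 months after switch | 8 | 8 | 8 | 6 | 3 | 0 | 5.50 |

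- Stopped at the switch: 4.17 − 1.67 = 2.5.
- Written rule, both arms read at six months: 6.17 − 5.50 = 0.67, a loss of (2.5 − 0.67)/2.5 = 73%.
- Written rule, unequal reading: control 5.5 or 4.5 against 5.5, a difference of 0.0 or −1.0.
- Written rule, both arms read three-monthly: a difference of 1.0 to 2.0, a loss of 20–60%.

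**Sensitivity.** If every intervention patient took the path without a detected drug level, with a switch at about 4 months (assumed), the untruncated difference stopped at the switch would be 5.5 − 4.0 = 1.5.

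**The case against.** A reader might infer that the protocol schedules the post-switch VL differently by arm. It does not: 5.2.4.1 and 5.2.4.2 carry the same six-month sentence. Unequal reading arises only if the control arm's retrospective testing extends past the switch, which the text neither states nor excludes. Section 6.1 can be read as using it only to fill in control VLs that were not taken before a switch. On the other side, viraemia in a switched patient ends after the switch, control plasma is still stored then, and the stated purpose is to find its duration.

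A reader might also infer that most of the effect is always hidden. With equal six-month reading and no truncation the mean difference is untouched. Only the ratio falls, from 5.5/2.0 = 2.75 to 11.5/8.0 = 1.44, and section 6.7.2 reports mean differences. The losses at month 24 treat time observed up to that point as the outcome. How censoring is handled may be set out in an analysis plan that is not shown. Patients who resuppress on first-line therapy get the same value under either definition.

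The strongest objection is that a stop at the switch is not neutral. Control patients are switched without resistance testing, while intervention patients without resistance stay on first-line therapy. Section 2.1 puts failure without resistance at 13–35%. The stop ends the clock for a control patient switched without resistance and lets it run for a comparable intervention patient. That stands, and it is why both durations should be reported.

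**Conclusion.** The point holds as a wrong stated rule. An outcome named for the failing regimen counts time on the next regimen, and its value depends on a post-switch reading rule that the protocol leaves open. If control retrospective testing reaches post-switch plasma, the claim of equal measurement frequency in 6.1 fails after a switch.

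Under the stated assumptions the size runs from no change in the mean difference (equal reading, no truncation), through 2.5 to 0.67 months (equal six-month reading, cut at month 24), to 1.5 or −1.5 months in place of 3.5 (unequal reading, no truncation). These figures illustrate the mechanism and are not forecasts.

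A reader might infer that the definition also corrupts the models. The documents do not support this. Section 3.2.3 names duration of viraemia as an input to the transmission model, and for that purpose viraemia after a switch belongs in the count, provided both arms are read alike. Section 6.3 does not name this duration as an input to the cost-effectiveness model. The outcome is an additional one and none of the three power calculations in 6.7.3 uses it, so the sample size is unaffected.

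**What to change.** 1. In 6.1, define time on a failing regimen as the time from the first VL above 1000 (including retrospectively tested samples) to the earlier of the first VL below 1000 on the same regimen and the date of switch to second-line therapy, censored at the last visit.
2. Name total duration of viraemia as a separate outcome, for use in the transmission model. State that it is read at the same post-switch time points in both arms, and say in 5.1.2 and 5.2.2 whether retrospective testing covers post-switch plasma.
3. Report the two durations together, so that a control switch made without resistance is not credited simply because it stops the clock.

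The first item costs one sentence and uses dates the study already holds. The second needs either a few VL assays on the stored plasma of switched intervention patients, or a limit on control retrospective testing so that the arms match. Visits and patient management stay as they are.

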### 5.2.2 Viral load determination

Quantitative measurement of plasma HIV-1 RNA (viral load) will be determined using a CE/IVD certified kit-based HIV-1 viral load assay, according to the instructions of the manufacturer. Batch wise retrospective analyses will be performed on stored plasma samples of patients with therapy failure in the control arm in order to determine duration of viremia. Results will be reported in copies/ml.

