#### 5.2.6 Dried Blood Spot-based Drug Resistance Testing

In case of a confirmed detectable viral load (>1000 copies/ml) in the presence of detectable drug level as indicated by DLM, a dried blood spot (DBS) sample acquired during the second viral load measurement will be sent to a WHO reference laboratory for drug resistance testing, where genotypic HIV-1 drug resistance testing will be performed using an RT-only assay optimized for non-B HIV subtypes. This assay has been validated for use on DBS and implemented in a pilot study at Ndlovu Medical Centre. The assay consists of a single-round one-tube RT-PCR to amplify the viral RT-gene between codons 40-238, followed by population sequencing of the amplified fragment in both directions using 2 primers only. With this approach all RT resistance information relevant to first-line regimens is generated at minimal cost for laboratory reagents, equipment and personnel. If resistance testing is indicated in patients using second line therapy, a protease-only genotypic assay will be performed on the DBS in addition to the RT-only assay. Drug resistance testing will also be performed retrospectively on stored DBS in all patients with therapy failure in the control group, using the same approach as described above. The WHO reference laboratory will provide the treating physician with the result and interpretation of the drug resistance test, containing viral subtype, a list of all mutations, specific indication of relevance of these mutations to drug-resistance, a drug susceptibility ranking using resistance interpretation algorithms, and an overall interpretation with treatment advice taking local availability of antiretroviral drugs into account.

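### Section 6.1 says retrospective testing gives both arms an equal measurement frequency, but stored control plasma is tested only in patients with therapy failure, so viraemia during follow-up is ascertained differently by arm

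*Protocol*

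**What the plan says.** Section 6.1 lists the virological outcomes, among them failure without resistance, unnecessary switches and time on a failing regimen. It then says that they can be compared because "VL and CD4 measurements will be performed retrospectively in the control group, resulting in an equal frequency of measurements between both arms".

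The procedures elsewhere in the protocol are narrower:

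- Scheduled VLs, control arm (5.1.2): "Viral load measurements will be performed at month 12 and 24 after start of ART", or at the same months after the last VL for patients already on ART.
- Scheduled VLs, intervention arm (5.1.3): "This strategy consists of 3-monthly VL monitoring at month 9, 12, 15, 18, 21 and 24". The VL row of Table 4 agrees: months 9, 15, 18 and 21 are marked for the intervention arm only.
- Retrospective VLs, control arm (5.1.2): "Retrospective VL testing on stored EDTA-derived plasma in case of clinical therapy failure, in order to retrospectively examine the duration of viremia". Section 5.2.2 repeats the limit: "Batch wise retrospective analyses will be performed on stored plasma samples of patients with therapy failure in the control arm".
- Retrospective genotyping, control arm (5.2.6): "Drug resistance testing will also be performed retrospectively on stored DBS in all patients with therapy failure in the control group".
- CD4: Sections 5.1.2 and 5.1.3 add one month-6 measurement in each arm. Table 4 schedules CD4 at months 6, 12 and 24 without separating the arms.

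No section provides for testing the stored plasma of controls who are not classed as failing. Plasma is stored for every control at every three-monthly visit.

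**The concern.** Section 6.1 starts the clock for time on a failing regimen at the first VL above 1000 copies/ml, and the Summary counts it per patient with therapy failure. Who enters that comparison therefore depends on when VL is measured. Intervention patients are screened at six visits, controls at two. A control who becomes viraemic after one scheduled VL and is suppressed again by the next is not classed as failing, so the stored samples that would show the episode are never tested. The same episode in an intervention patient is found.

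Long episodes are more likely than short ones to span month 12 or month 24, so the control failures form a length-biased sample. Three outcomes are exposed: time on a failing regimen per failing patient, the rate of viraemia during follow-up, and the rate of failure without resistance during follow-up. The statement that ought to warn the analyst of this instead says that the problem has been solved.

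**Working it through.** **1. The stated figure: equal VL frequency (ratio 1.0).** Inputs: 300 patients per arm; six post-randomisation VLs in the intervention arm (5.1.3) and two in the control arm (5.1.2); a control with therapy failure also has months 9, 15, 18 and 21 tested, making six; failure rate f = 20% (6.7.3). Call-back VLs, losses and the changed VL schedule after a switch are left out.

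- Intervention: 300 × 6 = 1,800.
- Control: 300 × [2(1 − f) + 6f] = 240 × 2 + 60 × 6 = 840, which is 840/300 = 2.8 per patient.
- Ratio: 840/1,800 = 0.47, not 1.0.

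| f | Control VLs | Ratio to 1,800 |
|---|---|---|
| 5% | 660 | 0.37 |
| 15% | 780 | 0.43 |
| 20% | 840 | 0.47 |
| 30% | 960 | 0.53 |
| 100% | 1,800 | 1.00 |

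The statement holds only if every control fails. This step uses protocol figures alone, apart from the other values of f.

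**2. Chance that an episode is picked up.** Assumption: one episode of d months, with onset uniform over the 18 months from month 6 to month 24. A VL at month t meets the episode if onset lies in the d months before t. For controls the chance is [min(d, 6) + min(d, 12)]/18. In the intervention arm it is 1 for any d of 3 months or more. If control failure also needs a second high VL two months later, replace d by d − 2.

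| d (months) | Intervention, any VL | Control, any VL | Control, confirmed |
|---|---|---|---|
| 3 | 1.00 | 6/18 = 0.33 | 2/18 = 0.11 |
| 6 | 1.00 | 12/18 = 0.67 | 8/18 = 0.44 |
| 9 | 1.00 | 15/18 = 0.83 | 13/18 = 0.72 |

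**3. Direction of the bias with no true effect.** Suppose half of episodes last 3 months and half last 9 months in both arms, and one VL above 1000 defines failure in both. Mean full length of the episodes found:

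- Intervention: (3 + 9)/2 = 6.0 months.
- Control: (0.33 × 3 + 0.83 × 9)/(0.33 + 0.83) = 8.5/1.17 = 7.3 months.

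The difference comes only from who is counted. The episode lengths here are illustrative.

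**4. Share of viraemic controls missed, same definition in both arms.** Missed share = 1 − (proportion qualifying when screened at months 12 and 24)/(proportion qualifying when screened at all six visits). Assumptions: onset as above, some episodes persistent, the rest exponential with mean 3 months. Confirmation, where required, is at the call-back: one month later in the intervention arm, two in the control arm.

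- Half persistent: 20% missed, whether failure is a single or a confirmed VL.
- 80% persistent: 7% missed.
- Across the persistence assumptions tried: roughly 7–34%, the upper end at about 30% persistent.

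The protocol gives no episode durations, so these figures show a range and are not estimates.

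**The case against.** Several points on the other side are sound.

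- **Within failing controls, the grid is equal.** Stored three-monthly plasma lets duration be reconstructed for them as in the intervention arm, and the sentence follows outcomes that mostly concern failing regimens. It could be read as meaning only these patients. That stands for duration within those patients. It does not cure the selection of who is classed as failing, and the sentence is not limited in this way.
- **Some control episodes may be caught off schedule.** Section 5.2.3 allows VL tests prompted by clinical abnormalities. This narrows the gap but is not systematic.
- **Therapy failure is not defined consistently.** Section 2.1 ties it to a confirmed VL above 1000, Section 6.7.3 to a VL above 1000, and Section 5.1.2 uses the phrase clinical therapy failure without defining it. A reader who counts any single high VL in the intervention arm but only confirmed ones in controls would get 29% missed where matched definitions give 20%. The documents do not support mixing the definitions, so the larger figure should not be used.
- **The scope is limited.** A reader might infer that all viraemia rates are affected. The month-24 VL outcome in Section 6.7.3 is measured on schedule in both arms and is not. A reader might also infer bias in resuppression. The primary objective (3.1) concerns resuppression after intensified counselling, and an episode found later in stored plasma was never detected or counselled, so the missing tests are not shown to bias it. Bias in the transmission and cost models is possible, since duration of viraemia is an input (3.2.3), but neither its size nor its direction can be derived here.
- **CD4.** The documents do not show that scheduled CD4 frequency differs by arm. They show only that the retrospective CD4 testing named in Section 6.1 has no matching procedure.

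**Conclusion.** The equal-frequency statement in Section 6.1 is contradicted by Sections 5.1.2 and 5.2.2. On protocol figures, controls have about 2.8 VLs per patient against 6, and equality would require every control to fail. The justification for comparing the arms therefore fails for time on a failing regimen per failing patient, and for viraemia and failure without resistance during follow-up. The duration comparison tends to favour the intervention even with no effect.

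The VL counts rest only on the schedule and the 20% failure rate. The direction rests on control failure being found at months 12 and 24. The size of the bias rests on assumed episode durations and cannot be fixed from the documents. Time on a failing regimen is listed among the additional virological outcomes and is not a sample-size outcome, so the sample-size calculations are untouched.

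**What to change.** **Preferred.** Batch-test the stored month 9, 15, 18 and 21 plasma of all control patients. Apply one VL-based definition of failure to the three-monthly grid in both arms, and compare viraemic time over all randomised patients rather than per failing patient. State how time after a switch is counted, because the VL schedule changes then (5.2.4). Cost: at most 300 × 4 = 1,200 assays on plasma already stored. At 20% failure, 60 × 4 = 240 of these are already planned, leaving 960 extra. Because they are retrospective, they need not alter patient management.

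**If this is not done.** Delete the equal-frequency statement for both VL and CD4, define clinical therapy failure, limit the between-arm virological comparison to the common scheduled time points (months 12 and 24), and report time on a failing regimen as descriptive only. Cost: wording, and the loss of a formal duration comparison.

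**Avoid** the cheaper-looking rule of tracing back, in both arms, only patients with a VL above 1000 at month 12 or 24. The intervention itself changes who is viraemic at those months, so the rule is fair only if there is no effect. In an illustrative run (half of episodes persistent, the rest exponential with mean 3 months, intervention episodes ending three months after detection), a true intervention-to-control ratio of viraemic time of 0.53 appeared as 0.14.

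For CD4, either describe the retrospective testing meant in Section 6.1 or remove the reference to it.
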